**Wellbeing outcomes**					
**Total difficulties (SDQ)**	Linear hierarchical	Yes	Yes	• Total difficulties baseline score • Month of birth • Sex	Year 9
**Total difficulties (SDQ)**	Linear hierarchical	Yes	Yes	• Total difficulties baseline score • Month of birth • Sex	Year 8

### Interim analyses {21b}

There are two cohorts of pupils that are the focus of this trial; those pupils in intervention and control schools in years 8 and 9 at September 2020. Following training, it is anticipated that school Development Plans will reflect WSS processes and actions from September 2021. Longitudinally the year 9 cohort would capture the near-term effects of the intervention at GCSE, and the Year 8 cohort would capture the more medium-term effects.

Analysis of outcomes for the year 8 cohort will only proceed if acceptable implementation fidelity is achieved (determined by the IPE—see the ‘Discussion’ section). The results of the main phase of the research, focusing on students in year 9 as of September 2020, will be published in a report in January 2024. If the data from the main phase are robust, then the results of the additional phase of the research, focusing on students in year 8 as of September 2020, will be published in a report in February 2025.

### Methods for additional analyses (e.g. subgroup analyses) {20b}

Consistent with EEF’s analysis requirements [21], we will run a specification similar to that for the primary analysis, where the FSM indicator is interacted with the intervention group indicator variable and separately on the ever-FSM subsample. This will therefore be a full adjusted specification which includes a baseline measure of the dependent variable entered as a covariate at the pupil and school levels as well as further covariates for month of birth, sex and FSM.

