### Sample size {14}

Table 2 sets out the assumptions upon which we have based sample size calculations. It states the relevant minimum detectable effect sizes [12] associated with the primary analysis (SEND designated pupils only), analysis for all pupils (the sample upon which many secondary outcomes will be estimated) and subgroup estimates for pupils ever in receipt of Free School Meals (FSM; the main subgroup analysis).

**Table 2 Tab2:** Sample size calculations (calculated using PowerUp!^a^)

	All pupils	SEND pupils	FSM pupils
**Minimum Detectable Effect Size (MDES)**	0.19	0.20	0.19

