**Number of pupils**			
Intervention	14,400	2000	3360
Control	14,400	2000	3360
Total	28,800	4000	6720

^a^PowerUp! https://www.causalevaluation.org/power-analysis.html

The size of the anticipated sample available for this trial is influenced by the following factors:
The costs to the developer of working with schools and the available programme budget which determines the maximum possible size of the intervention group.The number of schools that the developer could reasonably be expected to recruit in the time available based on our experience of recruiting secondary schools to other similar EEF-funded studies.The average size of schools.The likely proportions of pupils within schools that are SEND and have ever qualified for free school meals.

In addition, our sample size calculations are based on a number of further assumptions in relation to:
The correlation between KS2 English raw scores and GCSE English marks.The intraclass correlation coefficient at the school level.Whether information on the class that individual pupils were in at randomisation for the teaching of English language is available, and if available, is reliable.

In addition to these factors, schools will be assigned to intervention and control groups on a 1:1 basis. Statistical tests will be conducted on the basis of two-sided tests of statistical significance with standard assumptions made regarding types I and II statistical error rates (5 and 20% respectively).

At the outset of the study, the developers informed the research team that they had a budget to work with around 100 schools. This implied the need to recruit some 200 schools to the trial such that subsequent to randomisation 100 schools would be assigned to the intervention. However, previous experience within the research team led to the conclusion that the developers would struggle to recruit 200 schools to this study in the time available. For example, the ‘Evaluating the effectiveness of Eedi formative assessment programme’ study, which also involved the recruitment of mainstream secondary schools to an EEF-funded trial, set out to recruit 180 schools, but despite the best efforts of the developers, only 158 schools agreed to take part in the trial [13]. Given this experience and the fact that the WSS Review will be more demanding on school resources in general, it was felt that 160 schools would be a reasonable but ambitious target that could be achieved by developers in the time available.

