With an achieved sample of some 160 schools we can obtain estimates for the average number of pupils in a given focal-year-cohort, the number of pupils that are likely to be SEND as well as the expected number of pupils that had ever qualified for free-school-meals:
Based on previous studies we expect on average six classes in each year group in mainstream secondary schools and each class will comprise approximately 30 students.Thus we expect to find on average about 180 students in each year-group cohort per school (and that there are two cohorts per school).Drawing on national publicly available estimates, we expect that around 14% of pupils to be designated SEND [2]. This means that on average we expect to find 25 SEND pupils in each year-based cohort per schoolNearly a quarter of pupils in maintained secondary schools have qualified for FSM at some point in their school careers [14]. This means we can expect around 42 pupils per cohort, per school to have been in receipt of FSM.

Given these estimates we anticipate that in some schools the numbers of pupils in our sample that will be both SEND and FSM will be very small. For this reason, the sample size estimates above are for all FSM, rather than SEND pupils that are also FSM. Likewise, as set out in the Statistical Methods section we do not propose estimating effects for that subgroup of SEND pupils that are also ever-FSM, due to anticipated small sample sizes.

We obtained an estimate of the correlation between KS2 Raw score for English and GCSE English language attainment from the analysis provided by the Education Endowment Foundation [15]. The assumption used for the intraclass correlation coefficient is 0.20 (proportion of the total variance at the school level), and though possibly conservative is the assumption used for many EEF-funded studies with GCSE attainment as a primary outcome.

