#### Primary analysis

Focusing first on the primary analysis, statistical estimates of the effect of exposure on marks at GCSE English will be obtained from a hierarchical linear model (the estimator), in which pupils are clustered within schools. This model will be fitted to data for SEND pupils only. Three regression model specifications are proposed, where the standardised or equated mark for each pupil is the dependent variable^1^, and the regression models include the following covariates:
*Model 1*: binary intervention group indicator coded to ‘1’ if the school is assigned to the intervention ‘0’ otherwise, plus regional fixed effects (representing strata).*Model 2*: As above, with KS2 Reading raw score as a covariate expressed as a departure from the school mean for each pupil at the pupil level, and as a school average departure from the overall mean at the school level*Model 3*: As model 2, with additional covariates representing sex, month of birth, unauthorised absences in the year prior to randomisation and FSM variables.

The effect size, consistent with Hedges’ *g*, will be obtained from model 2, as set out in EEF guidance [20]. The effect size parameter is written:
$$ ES=\frac{\mu^T-{\mu}^c}{\sqrt{\sigma_i^2+{\sigma}_j^2}} $$

A sample estimate of *μ*^*T*^ − *μ*^*c*^, where *μ*^*T*^ is the mean of the outcome in the treatment group and *μ*^*c*^ the mean in the control group, is derived from the coefficient obtained on the binary intervention group indicator from model 2 above. The denominator $$ {\sigma}_i^2+{\sigma}_j^2 $$, where *i* indexes for the school and *j* the pupil, are the variances at the school and pupil levels respectively, such that the intraclass correlation coefficient is $$ {\sigma}_i^2/{\sigma}_i^2+{\sigma}_j^2 $$. A sample estimate for the denominator is obtained from the total unconstrained pooled variance as described in Hedges [20], who also provides an equation for the variance of the sample estimate for the effect size. Uncertainty will be assessed through computation of 95% confidence intervals and *p* values.

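### The FSM-by-intervention interaction, read as the primary random-intercept model plus one term, leaves between-school variation in the FSM gap out of its standard error and can exceed a 5% error rate

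*Protocol article*

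**What the plan says.** The section on additional analyses {20b} gives the FSM analysis two parts. The first is an interaction model: "we will run a specification similar to that for the primary analysis, where the FSM indicator is interacted with the intervention group indicator variable". The second is a fit of the same kind "and separately on the ever-FSM subsample". The section then lists covariates: the baseline measure at pupil and school levels, month of birth, sex and FSM. It does not mention random effects or the type of standard error.

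The model it refers back to is set out under Primary analysis. Estimates are "obtained from a hierarchical linear model (the estimator), in which pupils are clustered within schools". The two components in the effect-size denominator "are the variances at the school and pupil levels respectively", and the intraclass correlation is built from those two alone. No slope variance is named.

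Sample size {14} refers to "subgroup estimates for pupils ever in receipt of Free School Meals (FSM; the main subgroup analysis") and gives the FSM column of Table 2 a minimum detectable effect size (MDES) of 0.19 with 42 pupils per school. The same section says "we do not propose estimating effects for that subgroup of SEND pupils that are also ever-FSM", which points to all pupils, not SEND pupils only, as the population for the FSM work.

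**The concern.** The interaction crosses levels: the arm is assigned to the school and FSM belongs to the pupil. It is estimated by comparing the within-school FSM gap between intervention and control schools. A school intercept shifts FSM and non-FSM pupils equally, so it drops out of that gap. A random-intercept model therefore handles clustering for the main effect of the intervention but not for the interaction. It treats pupil-level residual noise as the only source of uncertainty in each school's gap.

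If the gap also varies between schools, that variation belongs in the standard error, and the number of schools limits the precision. The article gives some reason to expect variation. Under Intervention description, each intervention school writes its own development plan with three areas for development, and the process evaluation is to study how much those plans differ. Schools may also differ in their FSM gap regardless of the programme.

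At stake is a funder-required statement on whether the Review works differently for disadvantaged pupils. An understated standard error could support a claim of a differential effect where there is none.

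**Working it through.** **Inputs, from Sample size {14} and Table 2.** 160 schools, 80 per arm; 180 pupils per school per cohort, of whom 42 are FSM, leaving 180 − 42 = 138 non-FSM; 25 SEND pupils per school; school ICC 0.20; pre/post correlations 0.70 (pupil) and 0.32 (school); two-sided alpha 0.05; power 0.80.

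**Step 1: reproduce the plan's own figures.** With squared correlations 0.49 and 0.1024 and 157 degrees of freedom,

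MDES = (t₀.₉₇₅ + t₀.₈₀) × √[0.20 × (1 − 0.1024) × 4/160 + 0.80 × (1 − 0.49) × 4/(160 × n)].

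This gives 0.190 for n = 180, 0.197 for n = 25 and 0.194 for n = 42, against the stated 0.19, 0.20 and 0.19. The inputs are therefore being read as the authors used them. These are main-effect figures; the article gives none for the interaction.

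**Step 2: the interaction standard error under a random intercept.**
- Pupil residual variance: 0.80 × 0.51 = 0.408.
- Sampling variance of one school's FSM gap: v = 0.408 × (1/42 + 1/138) = 0.01267.
- Difference between arms in the mean gap: variance v × (1/80 + 1/80) = 0.01267 × 4/160, so the model SE is 0.0178.

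**Step 3: let the gap vary between schools.** With between-school SD τ, the true variance is (v + τ²) × 4/160, while the model still reports v × 4/160. The SE is too small by the ratio R = √(1 + τ²/v), and the actual two-sided error rate at nominal 5% is 2 × [1 − Φ(1.96/R)]. The article does not give τ, so the values below are assumptions, in outcome SD units.

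| τ (assumed) | Model SE | True SE | R | Type I error | Simulated |
|---|---|---|---|---|---|
| 0 | 0.018 | 0.018 | 1.00 | 5.0% | 5.4% |
| 0.05 | 0.018 | 0.020 | 1.09 | 7.3% | 7.1% |
| 0.10 | 0.018 | 0.024 | 1.34 | 14.3% | 15.2% |
| 0.15 | 0.018 | 0.030 | 1.67 | 23.9% | 24.2% |
| 0.20 | 0.018 | 0.036 | 2.04 | 33.6% | 34.4% |

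The simulated column is from 1,000 simulated trials per row with a REML random-intercept fit, letting the FSM share vary between schools. Coverage of the nominal 95% interval is 100% minus the error rate: about 93%, 86%, 76% and 66% for τ from 0.05 to 0.20.

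**Step 4: the other possible population.** If the interaction model were fitted to SEND pupils only, assume 6 FSM and 19 non-FSM per school. Then v = 0.408 × (1/6 + 1/19) = 0.0895 and the model SE is 0.047. The error rates over the same τ values are 5.0%, 5.3%, 6.3%, 8.0% and 10.3%. Pupil-level noise is larger here, so the omitted variance matters less.

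**The case against.** The strongest reply is that the article does not say the slope is omitted. It promises a specification that resembles the primary one, lists covariates, and leaves the random part unstated. The two variances under Primary analysis appear in order to define the effect size and the ICC, not to describe the subgroup model. A condensed article may leave such detail to the full online protocol or an analysis plan, neither of which is shown. This stands to the extent that the missing slope is an inference. It does not remove the point: {20b} refers the analyst to a model whose variance components are named, and following that reference as written gives no slope.

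A reader might also infer that the interaction test is certain to be anti-conservative. The documents do not support that. At τ = 0 the error rate is 5%, the article gives no value of τ, and the upper rows of the table rest on assumed SDs. The relevant τ is also what remains after KS2 adjustment.

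Finally, a reader might infer that the whole main subgroup analysis is unsound. That goes too far. Table 2 sizes the estimate in ever-FSM pupils, and the separate fit on that subsample contains no cross-level term.

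**Conclusion.** The point holds in conditional form. Read as the primary model with an added interaction, the specification in {20b} forces the FSM gap to be the same in every school within an arm, apart from covariates and pupil-level noise. If that is not so, the interaction's interval is too narrow and its error rate is above 5%.

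On the better-supported all-pupil reading, modest variation is enough to matter: an assumed SD of 0.10 makes the true standard error 1.34 times the reported one. If only SEND pupils are used, the inflation is small over the same range. The figures assume equal school sizes, a normal approximation, the Table 2 inputs, and (for the SEND case) an FSM count the article does not state.

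Only the interaction test and its interval are affected. The primary analysis and the separate ever-FSM estimate are not.

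**What to change.** In {20b}, state that the interaction model includes a school-level random slope for FSM, with an unstructured covariance with the school intercept. If that model does not converge, use school-clustered robust standard errors for the interaction. If the full protocol or analysis plan already says this, the article needs only to refer to it. The same sentence should name the population for the interaction model (all pupils, or SEND pupils only), since the size of the problem depends on it.

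The change is one line and needs no new data. The cost is a somewhat wider interaction interval wherever the gap does vary: at τ = 0.10 the half-width goes from 1.96 × 0.0178 = 0.035 to 1.96 × 0.0238 = 0.047.

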### Methods in analysis to handle protocol non-adherence and any statistical methods to handle missing data {20c}

In order to perform instrumental variables regression and recover estimates of treatment effects, the point at which a unit is understood to have complied with their assignment needs to be determined. Given that the intervention is a whole school programme, pupils’ exposure is determined by school compliance. In order to use instrumental variables, we must also be sure that among other things, pupils in schools we declare to be non-compliant (among intervention schools) are not affected in any way by the intervention.

A conservative, minimal and therefore strict definition of compliance would be that schools assigned to the intervention that do not take up the 1-day SEND Reviewer training are non-compliant. Likewise, schools assigned to control that take-up training are also non-compliant. The only other source of exposure to WSS, outside the control of the developers, that a school assigned to control or intervention groups might be subject to, is downloading the intervention brochure/guidance from the developer website. In order to prevent this, the developer has removed the guidance and taken down the link for the duration of the study. Therefore we proceed on the basis that in order for an intervention school to be minimally compliant they must have received training. Likewise for a control school, they must receive no training. We propose to consult the developers’ records of training received in order to extract a measure of compliance.

There is a high chance that some schools recruited to the trial decide to withdraw, and this sample loss might both reduce precision of statistical estimates and introduce bias. Drawing on our experience and that of the developer, we will devise a strategy to limit school level attrition. Where attrition occurs, we will take steps during analysis to test various assumptions regarding missingness and assess to consequences for bias and precision. Other sources of missingness can result from misrecording of identifying data for pupils. This can be mitigated through carrying out extensive checks on students records at randomisation (see the ‘Plans for assessment and collection of outcomes {18a}’ section above). Where appropriate to do so, an assumption of missing at random will be explored through sensitivity analysis implementing multiple imputation.

### Plans to give access to the full protocol, participant level-data and statistical code {31c}

The full protocol was revised due to changes stemming from school closures in response to the COVID-19 pandemic. Version 2.0 (published on 30th October 2020) is available online^22^.

On completion of the trial, the participant level dataset will be made available within the EEF data archive within the ONS SRS. As per the EEF’s protocol, this will be done by FFT.

## Oversight and monitoring

### Composition of the coordinating centre and trial steering committee {5d}

#### Principal Investigators (Professors [name] and [name])

Design and conduct of trialPreparation of protocol and revisions; agreement of final protocolOrganising regular meetings between research team, developer and trial sponsorPublication of study reportsCompleting ethics committee applicationsBudget administration

#### Research team (protocol authors)

Study planningResponsible for maintenance of trial master file (baseline, SDQ and outcome data)Quantitative data verificationRandomisationQuantitative data analysisIPE data collection and analysis

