### Concealment mechanism {16b}

Allocation concealment will be achieved as randomisation will be conducted by computer, with school identifiers unknown to the research statistician running the randomisation script. Assignment status will be made known to all enlisted schools in June 2021.

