### Implementation {16c}

The researchers will assign schools to the intervention by the procedure outlined above (sequence generation).

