## Assignment of interventions: Blinding

### Who will be blinded {17a}

There are no specific measures for blinding. However, whilst the group assignments will be known to the researchers, data collectors, developers, SENDCos and other school staff, it is unlikely that pupils will be aware of the implementation of the intervention as distinct from other school activities.

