### Procedure for unblinding if needed {17b}

The design is open label so unblinding will not occur.

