### Composition of the data monitoring committee, its role and reporting structure {21a}

As the trial has been assessed to pose a minimal risk to pupils, a formal data monitoring committee is not required. However, the researchers will undertake review data on an ongoing basis as the trial progresses (particularly with regard to SDQ data) to monitor for any apparent adverse outcomes.

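### The outcome analyst is not masked to allocation: the research team that randomises also checks, monitors and analyses the data with the arm visible, and masking one analyst until data lock would be a cheap safeguard

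*Protocol article*

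**What the plan says.** All references are to the protocol article.

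- **Blinding (17a, 17b).** "There are no specific measures for blinding. However, whilst the group assignments will be known to the researchers, data collectors"; the sentence goes on to name the delivery team and staff in the schools as also aware of the arm. Item 17b adds: "The design is open label so unblinding will not occur".
- **Who randomises (16c).** "The researchers will assign schools to the intervention by the procedure outlined above". Under 16b there is masking at that one step, with "school identifiers unknown to the research statistician running the randomisation script".
- **Team roles (Research team, under 5d).** The list includes upkeep of the trial master file and "Quantitative data verificationRandomisationQuantitative data analysisIPE data collection and analysis" (spacing lost in the list). IPE is the implementation and process evaluation.
- **Data flow (18a, FFT under 5d).** FFT, a separate organisation, collects, verifies and prepares the baseline, SDQ and outcome data. The research team adds a second layer of checks.
- **Monitoring (21a).** There is no data monitoring committee; instead "the researchers will undertake review data on an ongoing basis as the trial progresses", with the SDQ singled out.
- **Missing data (20c).** Where attrition occurs, "we will take steps during analysis to test various assumptions regarding missingness". Multiple imputation is a sensitivity analysis, used where judged appropriate.
- **Year 8 phase (21b).** It depends on acceptable fidelity, as determined by the IPE, and on the main-phase data being robust.

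**The concern.** Open label is unavoidable for schools and delivery staff. It is not unavoidable for the person who prepares and runs the outcome analysis, and the reasoning in 17a does not address that person; beyond listing who knows the arm, it says only that pupils are unlikely to notice the programme.

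Blind marking protects the mark awarded to each script. It does not protect decisions taken after marks arrive: which queried records stay in, how missing outcomes are treated, and whether the data are good enough to support the next phase. Someone who knows the arm, and who may have seen SDQ data during the trial, can make these decisions in a way that leans towards one result without intending to. The article itself expects a high chance that some schools withdraw and says this may introduce bias, so the missing-data decisions may well matter. If they are made with the arm visible, a reader of the report cannot rule out that influence.

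**Working it through.** **1. Is this stated, or only left unsaid?** Item 17a says positively that no specific measures exist and that researchers know the arm. It is therefore a stated choice, not a detail left to an unseen analysis plan. A plan may fix the models in advance, but on this text whoever applies it can still see allocation.

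**2. Which steps are exposed?** Setting each step against what the article says:

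| Step after outcome data arrive | What the article says | Exposed to arm-aware judgement by the team? |
|---|---|---|
| Marking of scripts (Primary outcome) | Marked blind to trial status | No |
| Standardised marks (Primary outcome) | Obtained via schools from exam boards | Not shown |
| Record linkage (18a) | Linking variables named; who links is not stated | Not shown |
| First data checks (18a) | FFT, with school validation where Aspire is used | Not by this team |
| Second-level checks, and any exclusions that follow (18a) | Research team | Yes |
| Choice of model for the effect size (20a) | Fixed as Model 2 | No |
| Missing-data steps (20c) | Taken during analysis | Yes |
| Robustness of main-phase data (21b) | No criterion and no named judge in the article | Yes, if the team judges it |

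Three steps remain.

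**3. Can the size be calculated?** No. The documents give no rate of queried records, no attrition rate and no bias figure. What can be calculated is the precision against which a shift would be judged. Inputs from Table 2 and Sample size {14}: 160 schools, half per arm, 25 SEND pupils per school, ICC 0.20, pre/post correlations 0.70 (pupil) and 0.32 (school), two-sided alpha 0.05, power 0.80.

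Variance = ICC(1 − 0.32²)/(0.25 × 160) + (1 − ICC)(1 − 0.70²)/(0.25 × 160 × 25)
= 0.20 × 0.8976/40 + 0.80 × 0.51/1000
= 0.004488 + 0.000408 = 0.004896, so SE = 0.070 SD.

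MDES = 2.82 × 0.070 = 0.197, where 2.82 is the sum of the 97.5% and 80% t quantiles. This reproduces the stated 0.20.

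As a conversion only, a bias of b SD makes the two-sided error Φ(b/SE − 1.96) + Φ(−b/SE − 1.96). For assumed b of 0.02, 0.05 and 0.10 this is 5.9%, 11.0% and 29.8%. Nothing in the documents says that a bias of any of these sizes would occur.

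**4. Does masking the analyst cost power?** No. None of the inputs above changes, so the MDES stays at 0.197.

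**The case against.** The strongest reply is that this is a disclosed open-label design with a blind-marked external examination as primary outcome, and that masking the analyst is an extra safeguard rather than a requirement. That stands, and it limits the point to an improvement. The details of data lock, exclusions and missing-data methods may also sit in the full online protocol or an analysis plan, neither of which is shown. That stands for the details, but not for 17a, which says outright that no measures exist.

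Several stronger readings are tempting and are not supported:

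- **That the team decides how marks are equated.** The Primary outcome section says the standardised marks come via schools from exam boards.
- **That the team does the linkage, or is sole checker.** The linkage text names no one, and FFT prepares and first checks the data.
- **That one person holds every role.** The list describes a team; members may divide the work, though the article does not say so.
- **That SDQ data are compared by arm during the trial.** Item 21a speaks of watching for apparent adverse outcomes and mentions no comparison by arm.
- **That a free choice among three models and two missing-data approaches inflates the false-positive rate of the headline result.** Model 2 is fixed as the source of the effect size and multiple imputation is confined to sensitivity analysis, so that choice is not open and no inflation figure built on it describes this plan.

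A practical objection also stands. Deleting one variable does not mask people who stored the randomisation seed, run the IPE and read training records. Linkage of baseline data uses the school URN, so it cannot be done on recoded school identifiers. The fix has to allow for both.

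**Conclusion.** The concern holds in a limited form. The article states that researchers know allocation and gives the research team randomisation, second-level verification, ongoing data review and analysis. Three judgements after outcome data arrive are therefore open to knowledge of the arm: the second-level checks and resulting exclusions, the missing-data steps, and the view taken of main-phase data quality. The last assumes that the team makes that judgement, which the article does not say.

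The size of any bias cannot be derived from the documents, and the conversion in the working is not an estimate of it. The primary mark is well protected by blind marking and the headline model is fixed. This is a cheap improvement and not a defect that undermines the trial. That it is cheap is a judgement: no document gives a cost, but FFT already prepares the data, pupils already receive meaningless identifiers before analysis, and no sample-size input changes.

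**What to change.** Amend item 17a and the research team's role list to say:

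1. FFT completes linkage and supplies the outcome analyst with a linked file carrying recoded school identifiers and region, but no allocation or compliance variable.
2. The outcome analyst is an existing team member not involved in randomisation, the IPE or SDQ monitoring.
3. On that file the analyst completes the second-level checks, exclusions, missing-data decisions and analysis code, and records the judgement on whether the main-phase data are robust. The fidelity judgement stays with the IPE and cannot be masked.
4. Allocation and training records are merged only after a signed data lock.

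Item 17a says data collectors know allocation, so FFT's own preparation would not be masked; the gain is that the analyst's decisions would be. The cost is some division of roles within the existing team, a short data-lock record and a slightly later start to the comparative analysis. Sample size and power are unaffected.
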